### Dissemination and implementation

OPAL has a high potential for sustainable maintenance of the implementation of the SPICT-DE in the primary care setting. If SPICT-DE is applied successfully and evaluated positively, the implementation strategy can be extended to other care regions and federal states of Germany. It can be assumed that the application of SPICT-DE may lead to a systematic initiation of PC actions and a more accurate prescription of specialized PC in the primary care setting. To promote further implementation of SPICT-DE, different formats will be suitable: e.g. PC in undergraduate medical education, postgraduate further education in PC, specialized training in PC, online courses and quality circles. Integrating the results of OPAL in education and training for physicians, nursing staff and other health care professionals will increase the awareness for PC for patients with chronic progressive diseases.

Publication in peer-reviewed open access journals and presentation at national as well as international PC conferences will disseminate results and make them accessible for a broader audience. There are no publication restrictions. For communication of the trial results to the participants, a newsletter will be send to GPs as the main target group after each study phase.

Following a very practical approach, the transferability of interventions in OPAL can be considered as promising. The results of OPAL can easily be transferred to other care regions and federal states in Germany. Different patient groups, relatives, GPs and health care stakeholders involved in the provision of PC at the end of life may benefit from the innovation content of OPAL.

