### Study phases

OPAL comprises three phases and focusses on two different levels: (1) primary PC provided by GPs and (2) PC provided by different health care providers in the health region Hameln-Pyrmont in Lower Saxony. Figure 1 outlines all phases, work packages and the corresponding timeline. Table 1 is a Gantt chart with information on study phases, work packages and detailed timeline.

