### Phase I: exploration of usual practice (9 months)

In phase I, we explore the usual practice of care for patients with chronic progressive diseases in the last phase of life (baseline data collection, t_0_). Phase I comprises the following five work packages:Work package 1a: Guided expert interviews (*n* = 15) with health care stakeholders and PC providers of different settings focusing on infrastructure, collaboration, care experiences, and care situation.Work package 2a: Standardized written survey with GPs (*n* = 50) of 35 different single or group practices to give an insight into organization and quality of PC for patients in the last phase of life. For this purpose, we will use the German version of the General Practice End-of-Life Care Index (GP-EoLC-I) [31].Work package 3a: Guided after-death interviews with relatives (*n* = 25) of deceased patients of the 35 general practices focusing on how they experienced and perceived PC in the last phase of life in general and provided by GPs.Work package 4a: Analysis of clinical data of patients with chronic progressive diseases of the 35 collaborating general practices who died within a defined period of time. The analysis is based on key indicators (e.g. chemotherapy for cancer patients in the last month of life, number of hospitalisation and treatment days in the last six months of life, number of patients who died in the hospital) to evaluate the quality of care at the end of life [5].Work package 5a: Secondary data analysis of patients who died in a defined period of time before the intervention and were insured members of the Local Health Care Fund (AOK) in Lower Saxony. The analysis is based on key indicators to evaluate the quality of care at the end of life [5].

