### Phase II: intervention (12 months)

The intervention in phase II will take place at two levels: (1) in the 35 general practices and (2) in the health region Hameln-Pyrmont, including different health care stakeholders and PC providers. Phase II comprises the following two work packages:Work package 6 (intervention at the level of general practices): The study team will visit each GP and their practice teams for a standardized training in using SPICT-DE. To ensure a common understanding of the term “palliative care”, a definition based on the German guideline [3] and on the World Health Organization [32] will be given to each GP in hard copy. The user training will be performed (duration: approximately 15 min) to illustrate the application of the SPICT-DE according to the recommendations of the “Guide to use SPICT-DE in the community” [22] and using two exemplary case vignettes. GPs then will be asked to apply the SPICT-DE in daily practice during a period of twelve months in any patient that would visit the practice or would be seen in domiciliary visit regardless of their place of living (e.g. at home, nursing home or care facility) and that would meet the following inclusion criteria: age ≥ 18 years with at least one oncological or non-oncological chronic progressive disease according to the SPICT-DE. Patients with a specialized out- or inpatient PC approach or residents of hospices will be excluded. For each patient meeting the inclusion criteria, GPs will be asked to highlight all applicable indicators of the SPICT-DE. In order to monitor the indicators chosen by GPs, check boxes will be added for each indicator and recommended PC action listed in the SPICT-DE. There will be the opportunity to mention any additional action as a free-text answer as well. The decisions and procedures regarding the patients for whom SPICT-DE has been used will be documented in the practice documentation system. Monitoring visits will be performed quarterly for supervision of the implementation process and for reflection on the application of the SPICT-DE in daily practice routine. Both the monitoring visits and the reflection talks will be minuted for process evaluation (see phase III).Work package 7 (intervention at the level of the health region): The implementation of the SPICT-DE in general practices will be complemented by a publicity campaign (including flyers, newsletters and a local press campaign), multidisciplinary discussion panels and trainings for change agents in the health region. These activities shall inform stakeholders and health care providers at the interfaces of PC about OPAL and its intervention in general practices. The intervention at this level ought to optimise the collaboration of different health care providers and PC professionals as well as the intersectoral provision of care for patients at the end of life.

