
### Phase III: evaluation (15 months)

In phase III, process and outcome evaluation will give an insight into barriers, facilitating factors, effects of the intervention, and reveal information on possibilities for sustainable maintenance.Work package 8: This work package is part of the process evaluation. Protocols from the monitoring visits and reflection talks in the 35 general practices during the intervention (phase II) will be analysed. Results will give further information about the implementation process of the SPICT-DE in general practice and its practicability as well as efficacy in daily GPs’ practice.Work package 9: This work package is part of the outcome evaluation. GPs will be asked to fill out a single-page semi-structured questionnaire with six questions concerning alterations in the patients’ situation and the occurrence of any critical incidences for every patient after the first application of the SPICT-DE. A critical incidence is defined as e.g. acute crises in the disease progression, unplanned hospital admissions, changes in therapy, care, and living environment as well as death of patients. Furthermore, GPs will be asked to indicate for each patient if and if so which PC actions as recommended by the SPICT-DE were initiated. Analysis of the indicators of the SPICT-DE and of initiated PC actions will give further information on the effects of the intervention and the handling of SPICT-DE in daily practice.Work packages 1b-5b (follow-up, t_1_): These work packages will be performed in an equivalent way as described for the work packages 1a-5a of phase I (baseline data collection, t_0_): guided expert interviews (*n* = 15), standardized written survey with GPs (*n* = 50) of the 35 general practices, guided after-death interviews with relatives (*n* = 25) of deceased patients of the 35 general practices, analysis of clinical data of patients with chronic progressive diseases of the 35 collaborating general practices who died within a defined period of time, and secondary data analysis of patients who died in a defined period of time after the intervention and were insured members of the Local Health Care Fund (AOK) in Lower Saxony. Results of these work packages will allow the pre-post comparison.

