Primary outcome is an optimised care at the end of life delivered by GPs using the German version of the GP-EoLC-I (work package 2a/b). It contains 13 items about clinical aspects (four-stage Likert scale: 4 = in every case, 3 = in most cases, 2 = in some cases, 1 = rarely or never) and 12 items about organizational parameter of end of life care. The GP-EoLC-I showed good internal consistency (clinical care Cronbach’s α: 0.847; organization Cronbach’s α: 0.684). The overall index is built by summation of all 25 items and a sum score between 25 and 100 (Cronbach’s α: 0.850) [31].

Secondary outcome is an optimised care at the end of life seen from the perspective of bereaved relatives (work package 3a/b) and displayed in data of deceased patients (work package 4a/b). Amongst others, decisive aspects will concern the overall care situation, the involvement in decision making, in defining care goals and advance care planning, the preferred place of living at the end of life, and preferred place of death.

Optimisation of care for patients at the end of life will also be assessed considering approved key indicators to evaluate the quality of end of life care (work package 5a/b) [5]:Chemotherapy for cancer patients in the last month of life,Insertion of percutaneous endoscopic gastrostomy tube in the last three months of life,Number of hospitalisation and treatment days in the last six months of life,Number of patients with general outpatient PC treatments according to the German Uniform Value Scale (Einheitlicher Bewertungsmaßstab, EBM),Number of prescriptions for specialized outpatient PC and number of first prescriptions within the last three days of life,Average duration of general and specialized outpatient PC treatments,Number of patients who died in the hospital.

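### Newsletters reporting results go to the participating GPs after each phase, so at least one reaches them before they complete the self-rated t1 primary outcome

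*Protocol article*

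**What the plan says.** The dissemination section fixes purpose, recipients and timing in one sentence: "For communication of the trial results to the participants, a newsletter will be send to GPs as the main target group after each study phase".

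On the timeline, the Study phases section states that "OPAL comprises three phases and focusses on two different levels". The section headings give 9 months for phase I (baseline, t0), 12 months for phase II (intervention) and 15 months for phase III (evaluation). The follow-up work packages, including the GP survey WP2b, are in phase III: "These work packages will be performed in an equivalent way as described for the work packages 1a-5a of phase I". They include the "standardized written survey with GPs (*n* = 50) of the 35 general practices".

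On the endpoint, the Outcomes section says: "Primary outcome is an optimised care at the end of life delivered by GPs using the German version of the GP-EoLC-I (work package 2a/b". The GPs answer this questionnaire themselves. Its 13 clinical items are rated on a four-stage frequency scale, and the total runs from 25 to 100. Data analysis specifies a paired t-test of the pre-post difference. The design is pretest-posttest, and no control group is described for the GP survey.

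WP6 describes the practice-level intervention as training, twelve months of SPICT-DE use, and quarterly monitoring visits with reflection. WP7 adds a regional publicity campaign, which includes newsletters, to inform stakeholders and providers about the project. Neither lists feedback of study results to GPs as a component. The Challenges section discusses selection bias only. Nothing in the article holds results back from GPs until t1.

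**The concern.** The recipients of the results newsletter are also the only raters of the primary outcome. Phase I collects the baseline GP-EoLC-I, relatives' accounts of care and indicators from deceased patients' records. If results of that kind are returned to GPs before they rate themselves again, the feedback could change what they do, or only how they describe it, without SPICT-DE playing any part.

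The main research question is whether applying SPICT-DE improves care. A paired comparison within one group credits the whole pre-post change to whatever happened in between. If feedback of results is part of what happened but is not defined as part of the intervention, a positive result cannot be attributed to the tool as the question requires.

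**Working it through.** **Step 1. Order of events.** The phase lengths are 9 + 12 + 15 = 36 months, which matches the three-year project, so the phases run one after another. Counting from the project start:

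| Event | Earliest time |
|---|---|
| End of phase I, first results newsletter | month 9 |
| End of phase II, second results newsletter | month 9 + 12 = 21 |
| Phase III, containing the t1 survey (WP2b) | between months 21 and 36 |

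A newsletter sent at the end of phase I comes at least 12 months before any t1 survey. A newsletter sent after phase II falls at or after the start of phase III, and the text does not place it before or after WP2b. The count before t1 is therefore at least one and possibly two.

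**Step 2. The plan's own figure.** Inputs from Sample size calculation: n = 50 GPs, difference 4 points, SD 10, paired t-test, two-sided 5%, stated power about 80%. I read the SD as that of the paired differences.

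- Noncentrality = (difference / SD) × √n = (4 / 10) × √50 = 2.83, with 49 degrees of freedom.
- Power from the noncentral t distribution = 79.2%; the normal approximation gives 80.7%.

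The stated power is reproduced, and the newsletter point does not affect it.

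**Step 3. What a spurious shift would do (illustration only).** The documents give no size for a feedback or expectation effect, so a range is assumed. Suppose SPICT-DE has no effect and other influences raise the mean t1 score by b points. The same test then rejects with noncentrality (b / 10) × √50 = 0.707 × b:

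| Assumed shift b (points) | Noncentrality | Probability of a significant result |
|---|---|---|
| 0 | 0 | 5.0% |
| 0.5 | 0.35 | 6.4% |
| 1 | 0.71 | 10.7% |
| 2 | 1.41 | 28.4% |
| 3 | 2.12 | 54.8% |
| 4 | 2.83 | 79.2% |

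For scale, 1 to 2 points is 1/4 = 25% to 2/4 = 50% of the difference that the study is powered to detect. Two points corresponds to moving up one category on two items.

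The table shows how sensitive the test is to a shift of any origin. It does not estimate what a newsletter would do.

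**The case against.** The case on the other side is substantial.

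- **Two newsletters before t1.** A reader might infer that both certainly arrive before the t1 survey. The documents do not support that: the phase II newsletter and WP2b are not ordered in the text. In addition, the monitoring protocols (WP8) and the SPICT-DE documentation (WP9) are analysed only in phase III, so there may be little to report when phase II ends. This stands.
- **Content.** A reader might infer that GPs will learn which items scored low, or what the team hopes to find. The article does not specify the content beyond trial results, and an article may fairly leave that detail to a fuller document. No pre-post result on the primary outcome can exist before t1. This also stands. It leaves untouched the stated purpose of communicating results.
- **Unplanned co-intervention.** That label would be wrong. The newsletter is planned in the dissemination section, and WP7 names newsletters as publicity. What can be said is that feedback of results to GPs is not defined as an intervention component.
- **Small addition to an existing problem.** GPs know the aim, are trained, use the tool for a year and are visited quarterly. Expectation effects come mainly from the uncontrolled, unblinded design, and an embargo would leave most of them in place. The study also describes itself as an MRC phase I study. All of this is true and limits the weight of the point. However, training and visits are needed to deliver SPICT-DE, whereas sending results before t1 is not, so this share of the risk can be avoided.

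**Conclusion.** The point holds in a limited form. On the stated schedule, at least the phase I results newsletter, and possibly the phase II one, reaches the GPs before they complete the t1 GP-EoLC-I. Feedback of results is not declared as part of WP6. The paired t-test has no means of separating any effect of it on practice or self-rating from the effect of SPICT-DE.

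This rests on two readings: that the phase I newsletter is sent at about the end of phase I, and that it carries results, as its stated purpose says.

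The size of the bias is unknown. The rise from 5% to about 11% or 28% depends on an assumed shift of 1 or 2 points, and it should not be read as evidence that newsletters produce such a shift. Nor do the documents show that bias will occur. It is an avoidable risk added to expectation effects that the design already carries. Nothing in the plan's figures or choice of test is wrong on this account. The change is worth making because it costs little and protects the single primary outcome.

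**What to change.** Amend the sentence in Dissemination and implementation so that newsletters sent to GPs before WP2b contain only study progress and organisational information. Phase I and phase II results should be released to the participating GPs only after the t1 GP-EoLC-I has been returned.

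If results have already been sent, describe the feedback as a component of the intervention, and name it as a limitation on attributing the pre-post change to SPICT-DE.

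The WP7 publicity material need not change: it is a defined part of the regional intervention, and the article does not say that it carries results.

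The cost is one edited sentence and later results for the GPs. Sample size, power and analysis are unaffected.

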## Data Availability

Data collected during study application are available from the corresponding authors on reasonable request. Datasets from the Local Health Care Fund Lower Saxony were generated and analysed during the theoretical phase of this study and are not publicly available due to regulations of data privacy protection.

## Abbreviations

AOK: Local Health Care Fund
EBM: Uniform Value Scale (Einheitlicher Bewertungsmaßstab)
GP: General practitioners
GP-EoLC-I: General Practice End of Life Care Index
MRC: Medical Research Council
OPAL: Optimal care at the end of life
PC: Palliative care
SPICT-DE: German version of the Supportive and Palliative Care Indicators Tool
SPICT™: Original Version of the Supportive and Palliative Care Indicators Tool
